### Exclusion criteria

The exclusion criteria were failure to complete the questionnaire completely and unwillingness to continue the study.

### Scales and data collection

Quantitative data will be collected using 5 questioners, including:
**Sociodemographic characteristics questionnaire:** consisted of questions about the women and their husband’s ages, women and their husband’s education, number of pregnancies, number of deliveries, gestational age, weigh, height, Number of prenatal care.2-**Fear of COVID-19 Scale (FCV-19S):** This scale which is provided by Ahorsu and et al. [23], includes seven items. The participants indicate their level of agreement with the statements using a five-item Likert type scale. Answers included “strongly disagree,” “disagree,” “neither agree nor disagree,” “agree,” and “strongly agree”. The minimum score possible for each question is 1, and the maximum is 5. A total score is calculated by adding up each item score (ranging from 7 to 35). The higher the score, the greater the fear of coronavirus-19. More specifically, reliability values such as internal consistency (α = .82) and test–retest reliability (ICC = .72) were acceptable.3-**Corona Disease Anxiety Scale (CDAS):** This questionnaire has been developed by Alipour et al. in Iran [24]. The final version of this scale has 18 items and 2 components. Items 2 to 8 measure psychological symptoms and items 9 to 18 measure physical symptoms. The instrument is rated on a 4-degree Likert scale (never = 0, sometimes = 1, most of the time = 2, and always = 3); Therefore, the highest and lowest scores obtained by the respondents in this questionnaire are between 0 and 54. Higher scores in this questionnaire indicate a higher levels of anxiety in individuals. The reliability of this tool was obtained using Cronbach’s alpha method for the cause of psychological symptoms (0.879), for physical symptoms (0.861) of the first questionnaire (0.919).4-**Perceived Stress Scale (PSS):** which is provided by Cohen et al. [25] in 1983 with 3 versions of 4, 10, 14 that was applied for measuring perceived stress in past 1 month. We chose to use version 14 in this study. Each question has 5 options that half of them are direct (0, 1, 2, 3, 4), and the other half are reverse (4, 3, 2, 1, 0) scoring formats. All items are based on the Likert scale (0 = never, 1 = low, 2 = moderate, 3 = much, 4 = very much) scoring. Scores are ranged from 0 to 56 sets. It should be noted that 7 questions as positive concepts (4, 5, 6, 7, 9, 10, 13) are reverse (4 = never, 3 = little, 2 = moderate, much = 1, too much = 0). Reliability of PSS test was 0.85 and internal consistency of this test was calculated of 0.84 to 0.86 (43, 42). The homogeneity coefficients of this questionnaire in the Iranian population were also confirmed by Harris and Mousavi with the Cronbach’s alpha was 0.84 [26].5-**Pregnancy Self-Care questionnaire:** It consists of 13 questions that are rated on a 4-degree Likert scale (never = 1, sometimes =2, most of the time = 3, and always = 4). The reliability of the questionnaire in the internal consistency method, Cronbach’s alpha is 0.85 [18].

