### Objectives of the second phase: quantitative study

To determine self-care behaviors among pregnant women during the COVID-19 pandemic.To determine fear of COVID-19 among pregnant women during the COVID-19 pandemic.To determine anxiety of COVID-19 among pregnant women during the COVID-19 pandemic.To determine perceived stress among pregnant women during the COVID-19 pandemic.To determine the association between fear of COVID-19 with self-care behaviors.To determine the association between anxiety of COVID-19 with self-care behaviors.To determine the association between perceived stress with self-care behaviors.

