### Sample size and sampling method

Considering an acceptable error of 0.1 around the mean (m = 2.14), 95% confidence coefficient, 90% statistical power, and the standard deviation of 1.11 related to fear of COVID- 19 [21], the necessary sample size was determined to be 103 pregnant women, and regarding 95% confidence coefficient, 90% statistical power, an acceptable error of 0.05 around the mean (m = 71.9), and the standard deviation of 11.48 related to self-care, also an acceptable error of 0.05 around the mean (m = 60.27), and the standard deviation of 13.12 related perceived stress [18], the necessary sample size was determined to be 40 and 73 pregnant women, respectively. Also, Considering 57% anxiety with an acceptable error of 0.1 [22], the necessary sample size was determined to be 130. As the sample size based on anxiety was greater, this was the sample size sought. Regarding cluster sampling and design effect of 1.5, the final sample size was considered to be 215 pregnant women.
$$ n=\frac{{\left({Z}_{1-\frac{a}{2}}\right)}^2x\;p\left(1-p\right)}{d^2} $$

Sampling will be conducted in the healthcare centers in Tabriz. There are 82 public healthcare centers (*n* = 40) and posts (*n* = 42) in different regions of the city that provide primary care services, free of charge. Most of the pregnant women have health records in these healthcare centers and posts. A two-stage cluster sampling will be carried out so that 13 healthcare centers and 14 healthcare posts were selected using a randomizer software (www.random.org). A list of all pregnant women at each center will be extracted from the health records and the samples will be randomly selected from the ordered numbers. Afterward, using the phone number registered in each record, the researcher will call the potential participants and will invite them to participate in the study and will visit them in their homes if needed. Eligible participants will be provided with full explanations about the study objectives and procedures. Also, informed consent will be obtained before collecting information, and the importance of honest answers to the questionnaire will be emphasized, and they are asked to complete the anonymous questionnaires in a private room. A number of participants are likely to be illiterate, so the questionnaires will be completed by the researcher in order that the data collection method to be the same for all individuals.

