### Inclusion criteria

The inclusion criteria consisted of 1) Iranian nationality, 2) residency in Tabriz, 3) ability to read and write, 4) intention to participate in the study, 5) single pregnant women with the age range of 18–40 years, 6) pregnancy over 10 weeks, 7) no history of stressors in the last 6 months (e.g., divorce, death of a family member, and diagnosis of a family member with an incurable or life-threatening disease), 8) Having any disease or medical, obstetric risk factor identified on the basis of the family’s health records or, as the pregnant woman claims, also requiring special care or relative or absolute rest for the mother.

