
### Data analysis

SPSS-22 software is used to analyze the quantitative data. Sociodemographic, FCV-19S, PSS, CDAS and scoring of Pregnancy Self-Care questionnaires score will be described by frequency (percent), as well as mean (standard deviation) if the data are normally distributed. The association between Sociodemographic, FCV-19S, PSS, CDAS with Pregnancy Self-Care will be determined using the independent test, ANOVA and Pearson correlation tests in the bivariate analysis, and logistic linear regression adjusting the confounding variables in the multivariate analysis.

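### The unadjusted test of number of prenatal visits against self-care mixes attendance with gestational age (minor)

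*Protocol article*

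**What the plan says.** All of this is in the second (quantitative) phase of the protocol article.

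- **Scales and data collection.** The sociodemographic questionnaire ends with "number of pregnancies, number of deliveries, gestational age, weigh, height, Number of prenatal care". Gestational age and visit number are separate items. No reference period, definition or scaling of the visit number is given.
- **Inclusion criteria.** The gestational criterion is "pregnancy over 10 weeks", with no upper limit.
- **Data analysis.** "The association between Sociodemographic, FCV-19S, PSS, CDAS with Pregnancy Self-Care will be determined using the independent test, ANOVA and Pearson correlation tests" is the bivariate step. It is followed by "logistic linear regression adjusting the confounding variables in the multivariate analysis", and no confounder is named.
- **Objectives of the second phase.** The association objectives are of the form "To determine the association between fear of COVID-19 with self-care behaviors", and likewise for anxiety and perceived stress. None names visit number. The study design section does state a wider aim, to assess factors affecting self-care behaviours.

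**The concern.** Visits accumulate as pregnancy advances. Suppose, for illustration, that scheduled visits accrue evenly to 8 at 40 weeks. A woman interviewed at 12 weeks who has missed nothing has 8 × 12/40 = 2.4 expected visits. A woman at 38 weeks who has attended half has 8 × 38/40 × 0.5 = 3.8. The poorer attender has the higher count.

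Two things can follow when such a count is tested alone against self-care:

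- **Dilution.** Differences in gestational age act as noise in the count, and a real link between attendance and self-care looks weaker than it is.
- **Confounding.** If self-care itself changes over pregnancy, the count picks up that change and can show an association that has nothing to do with attendance.

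Reduced attendance is part of the study's motivation, and the second-phase results go to the expert panel in the third phase. A visits–self-care figure could be read there as a statement about attendance.

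**Working it through.** The plan gives no figure on this point, so there is none to reproduce. The check asks how far the mechanism can go under stated assumptions.

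**Inputs from the article.** Sample size: "the final sample size was considered to be 215 pregnant women". Clustering: "Regarding cluster sampling and design effect of 1.5". Effective sample size is 215/1.5 = 143.

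**Assumed, because the article gives no values.** Gestational age G is uniform over 10 to 40 weeks and independent of attendance A. Two models for the visit count C:

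- *Model A:* scheduled visits accrue linearly to 6, 8 or 10 by term; attendance fraction has mean 0.8 and SD 0.15 to 0.25, capped at 0 and 1.
- *Model B:* expected visits are 8 × (G − 6)/34, multiplied by a log-normal attendance factor with coefficient of variation (CV) 0.3 to 0.7. The correlation of self-care is set with log attendance.

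**Dilution.** If self-care S depends on attendance only, r(C,S) = r(A,S) × r(C,A).

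- Model A gives r(C,A) = 0.44, 0.52 and 0.59 for SD 0.15, 0.20 and 0.25. With r(A,S) = 0.30: 0.30 × 0.44 = 0.13 and 0.30 × 0.59 = 0.18.
- Model B gives a raw r of 0.16, 0.20 and 0.21 for CV 0.3, 0.5 and 0.7.

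Power (two-sided 5%, Fisher z) is approximately Φ(arctanh(r) × √(143 − 3) − 1.96), with √140 = 11.83:

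| r | arctanh(r) × 11.83 | power |
|---|---|---|
| 0.30 | 3.66 | 96% |
| 0.13 | 1.55 | 34% |
| 0.18 | 2.15 | 58% |
| 0.21 | 2.52 | 71% |

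**Confounding.** If S depends on gestational age only, r(C,S) = r(G,S) × r(C,G).

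- Model A gives r(C,G) = 0.75 to 0.87. With r(G,S) = 0.20: 0.20 × 0.75 = 0.15 and 0.20 × 0.87 = 0.17. Such values would reach significance in about 43% to 53% of studies at n = 143.
- Model B gives 0.10 to 0.17 for r(G,S) = 0.20, and 0.15 to 0.24 for r(G,S) = 0.30.
- The critical r is about 1.96/√212 = 0.135 at n = 215, and 1.96/√140.3 = 0.165 after the design effect. A spurious result can therefore cross the line, but need not.
- If r(G,S) = 0 and there is no attendance effect, raw r is 0.00. There is then no false association.

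**How much of the count is gestational age?** Share of count variance explained by G, for expected totals of 4, 8 or 12 visits by term under the Model B structure:

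| | CV 0 to 0.3 | CV 0.5 to 0.7 |
|---|---|---|
| no random visit noise | 62–99% | 26–41% |
| Poisson visit noise | 27–58% | 17–31% |

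**Effect of conditioning on gestational age (Model B).**

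| true correlations of self-care | raw r | partial r given G |
|---|---|---|
| attendance 0.3, gestation 0 | 0.16–0.21 | 0.25–0.26 |
| attendance 0, gestation 0.3 | 0.15–0.24 | 0.00 |
| attendance 0.2, gestation 0.2 | 0.24–0.26 | 0.16–0.18 |

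The partial correlation removes the spurious association and recovers most, not all, of the diluted one.

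**The case against.** The other side has four good arguments.

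1. **No objective asks about attendance.** Every association objective concerns fear, anxiety or perceived stress. Visit number appears once, on the background form beside weight and height. This stands, and it is why the point is minor. The wider aim of studying factors affecting self-care keeps it from being irrelevant.

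2. **The article does not say that the raw count will be correlated.** It names three bivariate tests for the whole block and does not assign one to visits. This stands in part: use as an unscaled count is the natural reading, not a stated fact. Grouping the count into bands would not remove the dependence on gestation.

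3. **A regression adjusting for confounders follows, and gestational age is on the form.** Gestational age is in the same bivariate block, so a link with self-care would itself be tested. At r = 0.20 that test has about 67% power at n = 143, against 43% to 53% for the spurious visits association. This is real but partial reassurance. No confounder is named. In the dilution case gestational age is unrelated to self-care, so choosing adjusters by their association with self-care would tend to leave it out, although including it helps. The unadjusted figure would be produced in either case.

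4. **A reader might infer that the test mostly reflects gestational age.** The article does not support that. The share of count variance due to gestation exceeds half only under some assumptions, chiefly fairly uniform attendance, and the article itself says the pandemic reduced attendance. Confounding also needs a relation between gestation and self-care that the article does not give.

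**Conclusion.** The point holds in a limited form. As written, the unadjusted visits–self-care association mixes attendance with gestational age. Under the assumed models a true correlation of 0.30 shows as about 0.13 to 0.21, and power at an effective 143 women falls from about 96% to between 34% and 71%. A spurious association of about 0.10 to 0.24 is possible if self-care correlates 0.2 to 0.3 with gestation. That condition is an assumption; without it the harm is dilution only.

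These sizes rest on uniform gestation from 10 to 40 weeks, linear accrual of visits, and attendance independent of gestation. None comes from the article.

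A reader might go further and conclude that the second phase answers the wrong question, or that the guideline rests on distorted evidence. The article supports neither: the fear, anxiety and stress objectives are not affected by how visits are coded, and nothing says that this one background test will be presented to the experts as evidence on use of prenatal care. Severity: minor.

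**What to change.** In the second-phase data analysis section, state that the association between visit number and self-care will be reported as a partial correlation given gestational age at interview. State also that gestational age will be a named adjuster in any multivariable model that contains visit number, whatever its own bivariate result.

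Both items are already on the form, so no new data are needed. The cost is one sentence in the plan and one adjustment term, and the visits result is no longer a simple bivariate figure comparable with the other background variables.

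An attendance ratio (visits attended divided by visits scheduled by that gestation) is an optional addition. It needs a visit schedule that the article does not give, and it is coarse for women early in pregnancy with only one or two scheduled visits.

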
### Data analysis

SPSS-22 software is used to analyze the quantitative data. Sociodemographic, FCV-19S, PSS, CDAS and scoring of Pregnancy Self-Care questionnaires score will be described by frequency (percent), as well as mean (standard deviation) if the data are normally distributed. The association between Sociodemographic, FCV-19S, PSS, CDAS with Pregnancy Self-Care will be determined using the independent test, ANOVA and Pearson correlation tests in the bivariate analysis, and logistic linear regression adjusting the confounding variables in the multivariate analysis.

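### The sample is drawn in 27 clusters with a design effect of 1.5, but the named analyses make no allowance for clustering, which overstates the precision of the descriptive estimates

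*Protocol article*

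**What the plan says.** Under Sample size and sampling method, the protocol article describes the first sampling stage: "A two-stage cluster sampling will be carried out so that 13 healthcare centers and 14 healthcare posts were selected". These come from 82 sites in the city (40 centres and 42 posts). The second stage is a random draw of women within each site: "A list of all pregnant women at each center will be extracted from the health records and the samples will be randomly selected". The clustering enters the sample size: "Regarding cluster sampling and design effect of 1.5, the final sample size was considered to be 215 pregnant women".

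Under Data analysis for the second phase, scores are to be summarised by frequencies, means and standard deviations. Associations with self-care "will be determined using the independent test, ANOVA and Pearson correlation tests in the bivariate analysis", and a regression adjusted for confounders follows in the multivariable step. The section names no centre effect, cluster-robust variance, survey procedure or sampling weight, and neither does any other section.

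Of the seven second-phase objectives, four are descriptive (levels of self-care, fear, anxiety and perceived stress). Three are associations of fear, anxiety and stress with self-care.

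**The concern.** A design effect of 1.5 is a statement that women from the same site resemble each other enough to raise the variance of an estimate by half. The independent-samples test, ANOVA and Pearson correlation, as named, treat all women as independent. The two sections therefore rest on different assumptions about the same data.

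Enlarging the sample does not resolve this. It restores the precision that clustering costs, but a standard error computed as if there were no clustering remains too small. Since the study was sized on precision at 95% confidence, interval width is the plan's own criterion. An interval from the naive formula would overstate how well the four levels are known, and these results go forward to the guideline phase.

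**Working it through.** **Inputs from the protocol article.** Design effect (DE) 1.5; final n 215; 13 + 14 = 27 clusters out of 82 sites; self-care SD 11.48, perceived stress SD 13.12, fear SD 1.11; anxiety proportion 0.57. No intracluster correlation (ICC) is given.

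**The plan's own sample size.**
- Means, n = (1.96 × SD / (relative error × mean))²: fear 103.4 (stated 103), self-care 39.2 (stated 40), stress 72.8 (stated 73). These reproduce when the error is read as a fraction of the mean.
- Anxiety, n = 1.96² × 0.57 × 0.43 / 0.1² = 94.2, so 95; the stated figure is 130.
- 130 × 1.5 = 195, not 215. An unstated further 10% would give 195 × 1.1 = 214.5.

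The anxiety figure and the final total therefore do not reproduce. That is a separate matter and does not weaken this point: reading the inflation as 215/130 = 1.65 makes the effect below slightly larger.

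**Implied ICC (equal cluster sizes assumed).** Mean cluster size m = 215/27 = 7.96. ICC = (DE − 1)/(m − 1) = 0.5/6.96 = 0.072.

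**Means and proportions.**
- Naive SE / correct SE = 1/√1.5 = 0.816, about 18% too small.
- Effective sample size = 215/1.5 = 143.
- Coverage of a naive 95% interval = 2Φ(1.96/√DE) − 1:

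| DE | Coverage |
|---|---|
| 1.25 | 92.0% |
| 1.5 | 89.0% |
| 1.65 | 87.3% |
| 2.0 | 83.4% |

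- With a first-stage finite-population correction: DE ≈ 0.928 + 7.96 × 0.072 × (1 − 27/82) = 1.31, and coverage is about 91%. This assumes that inference is limited to the 82 sites and that the 1.5 does not already include the correction.
- A simulation of 20,000 samples (215 women, 27 clusters, ICC 0.072) gave 89.3% coverage without the correction.

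**95% half-widths at n = 215.**

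| Quantity | Naive | With DE 1.5 | Planned margin |
|---|---|---|---|
| Self-care mean | 1.53 | 1.88 | 0.05 × 71.9 = 3.60 |
| Perceived stress mean | 1.75 | 2.15 | 0.05 × 60.27 = 3.01 |
| Fear mean | 0.148 | 0.182 | 0.1 × 2.14 = 0.214 |
| Anxiety proportion | 6.6 points | 8.1 points | 10 points |

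These are in the units of the planning SDs. The ratio of 1.22 does not depend on the scale. The corrected widths still meet the planned margins.

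**Associations.** Slope design effect = 1 + (m − 1) × ICC(outcome) × ICC(predictor), and type I error = 2(1 − Φ(1.96/√that value)):

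| Predictor ICC | Slope design effect | Type I error |
|---|---|---|
| 0.072 | 1.04 | 5.4% |
| 0.2 | 1.10 | 6.2% |
| 0.5 | 1.25 | 8.0% |
| 1.0 (constant within a site) | 1.50 | 11.0% |

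Simulated values were 5.7%, 6.0% and 11.1% at predictor ICCs of 0.072, 0.2 and 1.0. The predictor ICCs are assumptions, because the article gives none.

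**The case against.** The strongest reply is that the main inferences hardly move. Fear, anxiety and stress are scores on individual women, and for such predictors the inflation is small. That is correct, and it limits the point.

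A reader might go further and infer that the planned tests run at about 11% type I error. The documents do not support this. The 11% needs a predictor that is constant within a site. The questionnaire section lists ages, education, pregnancies, deliveries, gestational age, weight, height and number of prenatal visits, all of which belong to the woman or her husband. Centre versus post is not listed as a predictor. Education or visit counts may cluster by site, but the article does not say how strongly.

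It can also be said that the Data analysis section names no confidence intervals, so none can be called too narrow. This stands in part: the claim has to be conditional on intervals or standard errors being reported. Sizing on 95% precision makes that likely.

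The design effect is an unsourced allowance attached to the anxiety-based sample size, and applying it to all four outcomes is an assumption. This is why a range of coverage is given.

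Finally, an article may leave variance estimation to a fuller plan. That carries some weight for the regression, whose type and variance method are unclear. It carries less for the bivariate tests, which are named and which assume independence.

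**Conclusion.** The stated analysis does not match the stated design. At the plan's own design effect, any naive standard error for the four descriptive objectives is about 18% too small and a nominal 95% interval covers about 89%. The range is 92% to 83% for design effects of 1.25 to 2.0, and coverage is about 91% with a finite-population correction. The three psychological associations are only mildly affected, at about 5.4% to 6.2%. Sociodemographic covariates are affected more only if they cluster strongly by site; 11% is the upper bound at a design effect of 1.5.

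These figures rest on roughly equal cluster sizes, an ICC derived rather than stated, and the same design effect for every outcome. The change should be made, but the size of the effect does not put the study's central conclusions in doubt.

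**What to change.** Record the centre or post for each woman and revise the second-phase Data analysis section as follows.

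- **Means, proportions and their intervals:** use a design-based analysis (for example SPSS Complex Samples) with centre or post as the cluster and centre versus post as the stratum. Apply selection weights where women's selection probabilities differ. State whether a finite-population correction is used and for which target population.
- **Associations:** use the same design-based procedure, or a regression with a random centre intercept, or cluster-robust standard errors with a small-sample correction for 27 clusters. A linear mixed model should not be the method for proportions.
- **Reporting:** give the observed ICC and design effect for each outcome.

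The cost is revised wording, one recorded identifier and the site list sizes needed for weights. Intervals widen by a factor of about 1.22 at a design effect of 1.5. The plan already allowed for clustering in its sample size, so no additional women are needed on this account.

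### The only adjusted analysis of self-care is named as both logistic and linear regression, two incompatible models, although the article otherwise treats the score as continuous

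*Protocol article*

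**What the plan says.** In the second phase, Data analysis states that associations of the sociodemographic variables and the fear, stress and anxiety scores with self-care "will be determined using the independent test, ANOVA and Pearson correlation tests in the bivariate analysis". It then gives the adjusted step as "logistic linear regression adjusting the confounding variables in the multivariate analysis". No other adjusted analysis is named.

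Three of the second-phase objectives are associations with self-care, one each for fear, anxiety and perceived stress; the first reads "To determine the association between fear of COVID-19 with self-care behaviors". None defines a binary outcome such as adequate self-care.

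Of the self-care instrument, Scales and data collection says "It consists of 13 questions that are rated on a 4-degree Likert scale", with items scored from 1 to 4. It gives no total range, cut-off or category. Sample size and sampling method plans self-care from "an acceptable error of 0.05 around the mean (m = 71.9), and the standard deviation of 11.48 related to self-care". The same section describes two-stage cluster sampling of 13 healthcare centres and 14 posts, a design effect of 1.5 and a final sample of 215.

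**The concern.** A logistic model describes the log-odds of falling in a category. A linear model describes the mean of a numeric score. They need different forms of the outcome and answer different questions, so joining the two names leaves the estimand undefined. This is not a detail left to a fuller document: the article names the model and names it wrongly.

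The phrase covers the only confounder-adjusted answer to the three association objectives, and the quantitative results go to the expert panel that develops the guideline. Read as logistic, the analysis would need a split of the score that appears nowhere in the article. Its odds ratios could not be set beside the bivariate correlations and mean differences, and part of the information in the score would be discarded.

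**Working it through.** **1. How the article handles self-care elsewhere.**

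- *Planning.* Inputs from Sample size and sampling method: mean 71.9, SD 11.48, error 0.05, 95% confidence. Taking the error as a fraction of the mean, n = 1.96² × 11.48² / (0.05 × 71.9)² = 39.2, rounded up to the stated 40. The same formula gives 72.8 for stress (stated 73) and, with an error of 0.1, 103.4 for fear (stated 103). These are precision calculations for continuous means. They reproduce without a power term, although 90% power is mentioned; adding one would give 107 for self-care.
- *Bivariate tests.* Pearson correlation requires a numeric score. The independent test (presumably the t test) and ANOVA fit a numeric self-care score compared across sociodemographic groups.
- *Objectives and scale.* No category of self-care is defined.

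These places point to linear regression.

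**2. Illustrative cost of the logistic reading.** The article gives no effect size for an association, so correlations of 0.20 to 0.30 between a psychological score and self-care are assumed, with normal scores, one unadjusted predictor and two-sided alpha 0.05.

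- Power on the continuous score: Φ(atanh(r) × √(n − 3) − 1.96).
- Information kept after splitting so that a proportion q lies below cut-point c: φ(c)² / [q(1 − q)]. At the median this is 0.1592 / 0.25 = 0.64, so 215 women carry the information of about 137. At an 80/20 split it is 0.49, or about 105 women.
- Power after a split: the first formula with r multiplied by the square root of the information kept (0.798 at the median).

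Example at r = 0.20, n = 215: atanh(0.20) × √212 = 2.95, less 1.96 is 0.99, giving 84%. After a median split r becomes 0.160, and 2.34 − 1.96 = 0.38 gives 65%.

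| Assumed r | n = 215, continuous | n = 215, median split | n = 143, continuous | n = 143, median split |
|---|---|---|---|---|
| 0.20 | 84% | 65% | 67% | 48% |
| 0.25 | 96% | 84% | 86% | 67% |
| 0.30 | 99% | 95% | 96% | 82% |

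The n = 143 columns use 215 / 1.5 = 143, which assumes that the design effect applies in full to the association. A simulation at n = 215 and r = 0.20 (1,500 runs, no clustering) gave 85% for linear regression and 65% for logistic regression on a median split.

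**3. The range of the score.** Thirteen items scored 1 to 4 imply a raw sum from 13 to 13 × 4 = 52. The planning mean of 71.9 lies above 52, so the two sections do not describe the same scoring. The calculations in step 2 do not depend on the range.

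**The case against.** The strongest reply is that this is a slip of wording which the article itself resolves. The phrase sits beside Pearson correlation and ANOVA, self-care is planned from a mean and SD, and nothing mentions odds ratios or dichotomising. That stands as the best guess at the intention, and it limits the seriousness of the point. It does not make the sentence usable, because the named model still has to be corrected before anyone can follow it.

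A reader might infer more than the article supports in three ways:

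- *That the plan intends to dichotomise, or to choose a cut-off from the data.* It says neither. A cut-off, if one were wanted, could also stand in a fuller document that is not shown, so its absence is not a separate fault.
- *That a planned power of 90% would be lost.* The 90% is quoted within precision calculations for single means and is not used in them. No association is powered, and the power figures rest on assumed correlations, an assumed split and one unadjusted predictor.
- *That self-care runs from 13 to 52.* That is only the raw sum implied by the item scores, and it conflicts with the mean of 71.9.

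**Conclusion.** The point holds as a specification error: the only adjusted analysis of the three association objectives is given a name that joins two incompatible models. The article's own treatment of the score supports linear regression.

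The power cost is conditional. It arises only if the logistic reading is followed. With a median split the loss at 215 independent women is about 19 percentage points at r = 0.20, 12 at r = 0.25 and 5 at r = 0.30. Allowing fully for the design effect lowers the absolute figures and gives a loss of about 14 to 19 points over the same range. These numbers show why the wording matters; they do not measure a shortfall in the planned study. The correction should be made before analysis.

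**What to change.** In the second-phase Data analysis, delete the word logistic and replace the phrase with: *multiple linear regression of the continuous self-care score on the psychological scores, adjusted for the listed sociodemographic variables*. Whether fear, anxiety and stress enter together or in separate models is the investigators' choice, but the text should say which, because joint entry adjusts each score for the other two.

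In the same sentence, account for the two-stage cluster sample with a random intercept for centre or post, or with cluster-robust standard errors. The sample size assumes a design effect of 1.5 over 27 sites, and no analysis named in that section reflects it.

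If a binary outcome is in fact wanted, name logistic regression alone and state and justify the cut-off in advance. When editing, reconcile the scoring of the self-care questionnaire with the planning mean of 71.9.

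The cost is one or two sentences, with no new data and no change to the sample size.
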